### Outcome measures

#### Primary outcome measure

Circadian profiles of gene expression from saliva samples of healthy, physically active individuals to characterize the CR. The participants will be provided four saliva sampling home kits with which they can collect their data during the four different rounds (each round of sampling collection carried out over two consecutive days) within the suggested season (spring/summer or autumn/winter) batch, see section ‘*Study Design’* for further details. Time series analysis of 8 core-clock and clock-controlled genes, *BMAL1*, *PER2*, *CRY2*, *NR1D2*, *AKT1*, *SIRT1*, *IL6*, *PDHB*, *GAPDH* (Glyceraldehyde-3-Phosphate Dehydrogenase housekeeping gene/internal reference gene), will be measured to quantify CR characteristics with respect to phase, amplitude and mesor.

#### Secondary outcome measures

Analysis of the influence of sex on the CR by comparison of CR profiles of males and females. Investigation of the seasonality of CR by collection of saliva samples during two seasons (spring/summer and fall/winter). Analysis of the influence of age on the CR by comparison of CR profiles of younger probands (age between 13 and 18 years old) and profiles of older and younger adults, considering participants between 18–39 and 40–60 years old in separate groups.

#### Explorative outcome measures

Additionally, clock and clock-related genes will be measured using a nanostring nCounter SPRINT Profiler using gene expression panels (Homo Sapiens Metabolic Pathways and a custom designed panel based on Extended Core Clock Network [55]) in a subset of participants to allow a better comparison of aging associated alterations of CR expression. By hormonal measurement at two different times of the year, the correlation between core-clock gene expression, cortisol and melatonin measurements will be investigated. The correlation between circadian gene expression and physiological parameters (daily activity measurements, heart rate, sleep) obtained by fitness trackers provided to the participants, will be explored.

### Data management

The study team will archive the source documents for each participant, which consists of the informed consent forms, saliva sample collection form, electronic participant surveys, reports for melatonin concentrations and cortisol profile, exported activity data from fitness tracker and gene expression results. The questionnaire and medical history data are collected by the participants themselves using the REDCap application [56]. In addition, the participants are asked to collect information on the exact times of the saliva sampling and time of daily habits, such as wake/sleep, and meal times during the sample collection days. Each participant is provided a pseudonymized self-reporting sheet for this purpose.

The study will be carried out in accordance with the applicable data protection regulations. All personal data collected during the study is pseudonymized before it is further conveyed, i.e., the recipient cannot establish a connection between the data and the participant. For this purpose, each participant is assigned a 12-digit randomized number as participant ID, generated using the R sample() function. The identifying "pseudonym keys" are stored in a re-identification list and only accessible to the study management. All data will only be communicated and published in anonymized way so that it will not be possible to draw any conclusions regarding the identity of the subject. The pseudonymously personal reference to the clinical data will be deleted after 10 years of archive period.

### Safety considerations

This study is a non-interventional, observational study therefore a safety consideration plan is not applicable. All procedures involving human subjects were approved by Charité -Universitätsmedizin Berlin Ethics Committee (EA2/242/20).

### Statistical analysis plan

#### Descriptive analyses

All continuous variables will be summarized using the following descriptive statistics: n (non-missing sample size), mean, standard deviation, median, maximum and minimum. The number and percentages (based on the non-missing sample size) of observed levels will be reported for all categorical measures. All summary tables will be structured with a row for each point in time and subgroup (if relevant) and will be annotated with the total population size relevant to that table/subgroup, including any missing observations.

#### Analysis for primary endpoint

Amplitude, phase and mesor of the circadian data for the subgroups according to sex, age and season will be estimated per core clock gene using cosinor (harmonic) regression. The null hypothesis that there is no circadian rhythmicity (H_0_ = 0) is tested against the alternative hypothesis that a circadian rhythmicity pattern exists (H_A_≠0). The study is considered successful if rhythmicity is detected in some of the measured genes.

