#### Sample size estimation

Sample size calculation was performed based on *BMAL1* gene expression data from our previous work [34] assuming that all measurements follow a sinusoidal wave function $y_{i}=A\;sin\;(\omega (t_{i}+\phi ))+M+\varepsilon_{i}$, 1 ≤ i ≤ n whereby n is the total number of samples, $\omega =\frac{2\pi }{Period}$ the frequency of the sinusoidal wave, φ the phase shift, M the rhythm-adjusted mean (MESOR), and t_i_ the observed Zeitgeber time. ε_i_ is the error term for sample i. We assume ε_i_ are identically and independently distributed from $\varepsilon_{i}∼N(0,\sigma^{2})$, where σ is the noise level. The null hypothesis that there is no circadian rhythmicity (H_0_ = 0) is tested against the alternative hypothesis that a circadian rhythmicity pattern exists (H_A_≠0). Rhythmicity will be tested using the F-test which compares the fitted model against a restricted model. For details see please Cornelissen [39]. The study is considered successful if rhythmicity is detected in the measured core-clock and clock-controlled genes obtained from saliva samples. To account for multiple comparisons (comparisons between gender and age subgroups and various seasons, in total up to 10 comparisons) the type I error is set to 0.005 according to the Bonferroni correction to hold the global significance level of α = 0.05. Underlying the data of our previous study [34], an amplitude (A) of 1.11 is estimated for *BMAL1* gene expression and the standard deviation of residuals (s) is 1.36, which gives an estimate of the intrinsic effect height of r = A/s = 0.82.

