**Fig 2 pone.0293226.g002:**
[figure not shown]
Graphical illustration of sample size estimation for the study protocol. The plot illustrates the identification of CR parameters based on *BMAL1* gene expression, which is then used to determine of sample size values and corresponding test power. Dashed red line indicates the optimal sample size (N) that needs to be collected for the detection of significant results according to pre-determined thresholds (α = 0.005; power = 0.8; r = 0.82). Accordingly, by considering a dropout rate of 12% a sample size of 59 participants was determined as needed to successfully assess the null hypothesis.

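### The success criterion is worded two ways, with no gene count, named gene or deciding sample; the 80% power is for BMAL1 alone and the alpha does not correct for genes

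*Protocol article*

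**What the plan says.** The protocol article defines study success twice. Under *Sample size estimation*: "The study is considered successful if rhythmicity is detected in the measured core-clock and clock-controlled genes obtained from saliva samples". Under *Analysis for primary endpoint*: "The study is considered successful if rhythmicity is detected in some of the measured genes". Both follow the same pair of hypotheses, no rhythmicity against rhythmicity.

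The sizing rests on one gene: "Sample size calculation was performed based on *BMAL1* gene expression data from our previous work". Its inputs are amplitude 1.11, residual standard deviation 1.36, and hence an "intrinsic effect height of r = A/s = 0.82". On the test: "Rhythmicity will be tested using the F-test which compares the fitted model against a restricted model". Alpha is 0.005, which is 0.05 divided by up to 10 comparisons; these are described as sex, age and season comparisons. The result is 52 for 80% power, raised to 59 for 12% dropout.

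*Primary outcome measure* lists 8 target genes plus GAPDH as the reference gene. *Analysis for primary endpoint* estimates the rhythm parameters for each core clock gene in the sex, age and season subgroups. It mentions no pooled fit.

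**The concern.** The success rule decides whether the primary objective is declared met. As written it leaves three things open: how many genes must be rhythmic, which genes they are, and whether the decision is taken in the whole sample or in a subgroup. All three could be settled after the data are seen.

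Two other statements depend on the rule. The 80% power is the power of the study only if success means BMAL1. The global 0.05 is kept only if the number of chances to succeed matches the divisor of 10, and that divisor does not count genes.

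**Working it through.** **Inputs.** From *Sample size estimation*: A = 1.11, s = 1.36, r = 0.82 (1.11/1.36 = 0.816), alpha = 0.005, power 0.80, N = 52, dropout 12%. From *Primary outcome measure*: 8 target genes. From the sex, season and age groupings (three age groups under *Secondary outcome measures*): 2 + 2 + 3 = 7 subgroups. Comparing the Introduction's list of core-clock genes with the panel gives 4 core-clock targets: BMAL1, PER2, CRY2 and NR1D2.

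**Step 1: the plan's own figure.** The cosinor F-test has 2 and n − 3 degrees of freedom. With evenly spaced sampling its noncentrality is n·r²/2. At n = 52 this is 52 × 0.82²/2 = 17.48, and power at alpha 0.005 is 0.8002. The 52 reproduces. (The unrounded r = 0.816 gives 53, with power 0.795 at 52.) Dropout: 52/0.88 = 59.09, stated as 59. The 80% is therefore correct for one test on BMAL1.

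**Step 2: power under the possible readings.** The article gives no effect size for the other 7 genes and no correlations between genes. The independence figures below assume that every gene has BMAL1's r, so they are illustrations.

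| Success means | Independent genes | Under any dependence |
|---|---|---|
| all 8 | 0.8⁸ = 0.168 | at most 0.80 |
| at least 7 of 8 | 0.503 | – |
| at least 6 of 8 | 0.797 | – |
| at least 5 of 8 | 0.944 | – |
| at least 1 of 8 | 1 − 0.2⁸ > 0.9999 | at least 0.80 |

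The two bounds in the last column need only BMAL1 to be as assumed. All 8 rhythmic implies BMAL1 rhythmic, and BMAL1 rhythmic implies at least one. For 80% power on all 8 independent genes, each needs power 0.8^(1/8) = 0.9725. That takes N = 82, or 82/0.88 = 93.2, so 94 with dropout.

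**Step 3: false success when no gene is rhythmic, each test at 0.005, any one detection counting.**

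- Pooled sample, 8 independent genes: 1 − 0.995⁸ = 3.9%.
- Any of 7 subgroups, all tests treated as independent: 8 genes, 1 − 0.995⁵⁶ = 24.5%; 4 genes, 1 − 0.995²⁸ = 13.1%.
- The 7 subgroups are three ways of splitting the same data, so these tests overlap. Simulation with overlapping subgroups and independent genes gives about 22% for 8 genes and 12% for 4. A check run at 52 observations gave 3.2% per gene, hence 1 − 0.968⁸ = 22.9% and 1 − 0.968⁴ = 12.2%, the same within simulation error.

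Positive correlation between genes would lower all of these figures.

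**The case against.** **The two sentences need not conflict.** A reader might infer that the same data must be a success under one sentence and a failure under the other. That requires the sample size sentence to mean all the measured genes, and it does not say *all* or *each*. It can be read as naming the panel, with the analysis section adding *some*. This stands: a contradiction is not proven. On that reading, however, the rule has no threshold at all.

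**The low power figure is an extreme.** The 17% assumes independence and BMAL1's effect in every gene. The article plans 80% for BMAL1 only, and its Introduction describes the core-clock genes as linked by feedback loops. This stands: across the dependence cases considered the range is 17% to 80%. If *some* means at least one, 80% is a valid floor and the study is adequately sized.

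**The rule is not empty.** A reader might call the *some* version unfalsifiable. The 3.9% for the pooled sample contradicts that. The inflation arises only if one subgroup is enough, which the article neither says nor excludes.

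**Fewer fits than 8 × 7.** The fitting sentence refers to core clock genes, which gives 4 × 7 = 28 fits, not 56. The success sentence refers to measured genes. Both counts are therefore shown, and both exceed 5%.

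**No third rule in Fig 2.** Its caption says that "a sample size of 59 participants was determined as needed to successfully assess the null hypothesis". A reader might take this as another success criterion, but it describes only the adequacy of the sample size.

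**Condensed article, observational study.** A minimum gene count could sit in a fuller plan, and amplitude, phase and mesor are estimated whichever label applies. That limits the consequence. But the article itself states the rule twice, in different words, and claims a global error level that depends on it. The fault lies in what is stated.

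**Conclusion.** The point holds as a criterion left open, not as a demonstrated contradiction. The two sentences differ, and neither fixes a count, a gene or the sample that decides.

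The 80% is correct for BMAL1. It is an upper bound for an all-genes rule and a lower bound for an any-gene rule. The global 0.05 holds for one of 8 genes in the pooled sample (3.9%). It does not hold if any gene in any subgroup counts (about 22% for 8 genes, 12% for 4).

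The power illustrations assume BMAL1's effect in every gene. The false-success figures assume independent genes and the 0.005 level for each test. The rhythm estimates themselves are unaffected; what is affected is the meaning of the word *successful* and of the error level attached to it.

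**What to change.** State one rule, in the same words, under *Sample size estimation* and *Analysis for primary endpoint*: the study succeeds if BMAL1, the gene it was sized on, is rhythmic in the pooled sample by the cosinor F-test at alpha 0.005. Add the pooled fit to the primary analysis, which now mentions only subgroups. Report the other 7 genes and the subgroup fits as secondary tests, with Holm adjustment across genes.

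This needs a few sentences and no new data, and the existing power calculation then belongs to the stated criterion. The downside is that the success label covers one gene, whereas the primary objective is a multi-gene profile; that profile is still estimated and reported.

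If a rule of at least k of 8 genes is preferred, state k, say that it applies to the pooled sample, and give its power with the effect sizes and gene correlations assumed. That costs more, because the article gives neither for the 7 other genes.

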#### Analysis for secondary endpoints

Differences in CR and mean gene expression level between subgroups, with respect to sex, age, seasons and physical performance, will be evaluated by CircaCompare [57] to estimate and observe differences between CR, specific to the characteristic desired (mesor, amplitude and phase). The methodology proposed by Parsons *et al*. [57] will be used for exploratory purposes, and circadian curves will be estimated per individual and sampling round. Additionally, correlations between molecular data and physical exercise measurements, as well as for hormonal data (melatonin and cortisol) and activity data (smart-tracker) will be calculated.

#### Missing values and outliers

Missing values will not be imputed. Outliers will be identified by the data management team. According to the decision of the data management team and principal investigator, outliers will be kept in the database or set to “missing”. If a participant did not have an acute (oral or any other) infection at the time of recruitment, but developed an infection during study, the data originated from that round of saliva sampling will not be considered for the data analysis.

#### Development of machine learning analysis pipeline

We will correlate alterations in the gene expression profiles to other measurements collected. The generated data will be used to develop and optimize computational pipelines to accurately assess a parameter for CR-dependent variation in different subgroups of the study participants with respect to sex, age or season. Albeit the results should be further validated in future and larger cohort of studies, the output data can then be further processed to apply a feature selection criterion from the smart tracker data (e.g., heart rate or activity data), which in turn can be correlated with the participants’ other measurements (saliva gene expression data, hormonal data) for assessing their correlation, and used to optimize the machine learning pipelines to train computational models, and predict optimal timings for daily activities such as physical activity. Depending on the data distribution, supervised machine learning algorithms based on linear (e.g., linear discriminant analysis), nonlinear (e.g., classification and regression trees), or complex nonlinear (e.g., Support Vector Machine, SVM) methods will be used.

### Ethics statement

All procedures involving human subjects were approved by Charité—Universitätsmedizin Berlin Ethics Committee (EA2/242/20). The participants were enrolled on a voluntary basis and signed the informed consent approving the analysis of their data in the scope of the study.

### Status of the study and timeline of the study

The study started to recruit upon ethics approval, in 2022. The recruitment and data collection are planned to be carried out until the December 2023.

## Discussion

Circadian medicine has gained significant interest in recent years as the relevance of the circadian system in enhancing overall health and well-being has been recognized by researchers and healthcare professionals. However, there are several challenges hindering the application of circadian medicine into clinical practice. These obstacles include a lack of comprehensive understanding of the intricate mechanisms underlying CR, the need for substantial changes in clinical practices and infrastructure to accommodate circadian-based diagnostics and treatment schedules, and the absence of standardized, easy, and non-invasive approaches to characterize and CR.

Circadian regulation poses optimal time frames for daily activities, examples include meal times [58], hormone secretion [59], and cognitive performance [60]. Physical performance is also among circadian-influenced activities in which previous studies by our group and others pointed to a higher athletic performance reported in the afternoon hours compared to morning hours [34, 61, 62]. The core clock gene, *PER2* impacts the peak timing of exercise whereas the average expression of *BMAL1*, correlates with the muscle tone among healthy, physically active individuals [34].

To further investigate the above-described findings, this study aims to analyze circadian gene expression profiles from saliva samples to characterize CR in different individuals and identify variations based on factors like sex, age, and seasons. The data collected will contribute to a comprehensive understanding of CR profiles and can be correlated with hormonal assessment, questionnaires, and activity tracking to improve sleep, overall health, and optimize daily activities. As a prospective, the study intends to correlate molecular CR profiles with findings related to physical performance and develop computational models to predict optimal exercise timing for individuals with similar circadian rhythm profiles, which can be further validated in future studies. Such findings are not only useful for athletes, but also for patients undergoing physical rehabilitation, as well as for Parkinson’s Disease patients, where physical activity is used to slow down disease progression. The CR profiles collected can also be used to establish a control group of individuals with healthy CR, which may be used for future comparison between CR of individuals with different pathological conditions.

### Limitations of the study

Associated limitations to this study include limited generalizability to broader population groups due to specific inclusion criteria, and potential errors in saliva sample collection by participants despite efforts to minimize them. Nevertheless, this study’s sampling method can assess CR in healthy individuals, making it useful also in clinical and non-clinical settings for future monitoring of disease related to CR disruption, and for adapting daily activities to enhance the CR.

### Dissemination plans

Findings will be disseminated through peer-reviewed publication and via oral and poster presentations at national and international conferences and symposia.
